## Abstract

**Background:**

Globally, about 50 million people were living with dementia in 2015, with this number projected to triple by 2050. With no cure or effective treatment currently insight, it is vital that factors are identified which will help prevent or delay both age-related and pathological cognitive decline and dementia. Observational data have suggested that hearing loss is a potentially modifiable risk factor for dementia, but no conclusive evidence from randomised controlled trials is currently available.

**Methods:**

The HearCog trial is a 24-month, randomised, controlled clinical trial aimed at determining whether a hearing loss intervention can delay or arrest the cognitive decline. We will randomise 180 older adults with hearing loss and mild cognitive impairment to a hearing aid or control group to determine if the fitting of hearing aids decreases the 12-month rate of cognitive decline compared with the control group. In addition, we will also determine if the expected clinical gains achieved after 12 months can be sustained over an additional 12 months and if losses experienced through the non-correction of hearing loss can be reversed with the fitting of hearing aids after 12 months.

**Discussion:**

The trial will also explore the cost-effectiveness of the intervention compared to the control arm and the impact of hearing aids on anxiety, depression, physical health and quality of life. The results of this trial will clarify whether the systematic correction of hearing loss benefits cognition in older adults at risk of cognitive decline. We anticipate that our findings will have implications for clinical practice and health policy development.

**Trial registration:**

Australian and New Zealand Clinical Trials Registry (ANZCTR: 12618001278224), registered on 30.07.2018.

## Background

Hearing loss is the second highest cause of disability in the world, affecting 466 million people, with 90% of cases being due to age-related hearing loss (ARHL) [1]. ARHL is a highly prevalent form of sensory impairment in later life, affecting 40 to 45% of people aged 65 years and 83% of those aged 70 years or above [2]. ARHL increases the risk of mental health problems [3], frailty [4], cognitive impairment [5] and dementia [6].

Currently, more than 50 million people are living with dementia, and this is projected to reach 75.63 million in 2030 and 135.46 million in 2050 [7]. According to the Lancet Dementia Taskforce, of the many risk factors that contribute to dementia, hearing loss could account for 8% of all dementia cases [8]. Developing effective strategies to prevent dementia has become a global health priority, with projections suggesting that the total number of people living with dementia could be reduced by 13% if the onset of symptoms could be delayed by two years or more [9].

Australian data from the Health In Men Study showed that in a sample of 37,898 older men, the hazard of dementia associated with hearing impairment was 1.69 (95%CI = 1.54, 1.85) [10]. In addition, a systematic review of 14 prospective studies showed that hearing loss was associated with a 49% (95%CI 30–67%) increase in the hazard of dementia [10]. Whilst this data shows a clear association between hearing loss and cognitive impairment, a causal relationship cannot be definitively determined, and it is currently not known whether the correction of hearing loss through the use of hearing aids can decrease the rate of cognitive decline or reduce dementia risk.

Our trial aims to investigate whether the correction of hearing loss through the use of hearing aids (HAs) could decrease the 12-month rate of cognitive decline among older adults at risk of dementia.

## Methods

### Aims

This trial will determine whether the correction of hearing loss through the use of hearing aids (HA) decreases the 12-month rate of cognitive decline among older adults at risk of dementia.We will also investigate whether the correction of hearing loss has a beneficial impact on memory and executive functions, anxiety and depressive symptoms, quality of life, physical health, and health-related costs over 12 months.We will explore whether the expected clinical gains achieved through the correction of hearing loss by 12 months can be sustained over an additional period of 12 months and if losses experienced through the non-correction of hearing loss can be reversed with the fitting of HAs after 12 months (i.e., HAs fitting for controls at 12 months with follow up of 12 months).

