### Study design

Two-arm parallel randomised controlled trial.

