### Procedures for the collection of study measures

The procedure for the data collection will follow the Consolidated Standards of Reporting Trials (CONSORT) guidelines. During the screening process, participants who meet the criteria for inclusion in the study will be randomly assigned to either the experimental (A) or control (B) group. Group A participants will receive the intervention immediately after the baseline assessment, whereas group B participants will receive the intervention 12 months later (Fig. 1). All participants will be informed that if they get randomly allocated to group B, they will have to wait 12 months to receive the treatment. Those who prefer to receive HAs immediately without having to wait 12 months will be given the option to opt-out from the study. Cognition, mental health and QoL assessments will be carried out separately to the hearing assessments and HA fitting.

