**Fig. 1 Fig1:**
[figure not shown]
Anticipated participant recruitment flowchart

Group A will complete hearing assessment, cognitive, mental health and QoL assessment at the baseline, 6, 12, 18 and 24 months.

Group B will complete hearing assessment, cognitive, mental health and QoL assessment at the baseline, 6, 12 months, 18 and 24 months. (Primary endpoint analysis at 12 months and follow-up analysis at 24 months are shown in Fig. 1). Timeline of the study is shown in Table 1.

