### Statistical analysis

All analyses will follow CONSORT guidelines. We will use standard descriptive statistics to compare basic sociodemographic and clinical data across treatment arms. We will use multilevel mixed models to investigate changes in cognitive and other scale scores over time. Mixed models provide estimates that are “intention-to-treat’ and allow for the investigation of interactions between group and time effects, as well as for the adjustment of possible imbalances between the groups following the randomisation. We will use imputed chain equations if the loss to follow up exceeds 25%. All probability tests will be two-tailed.

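### From month 12 both arms have hearing aids, so the second year can compare early with delayed fitting but cannot determine that gains are sustained or losses reversed

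*Protocol article*

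**What the plan says.** The Study design section describes a "Two-arm parallel randomised controlled trial". The section on procedures for collecting study measures gives the timing: "Group A participants will receive the intervention immediately after the baseline assessment, whereas group B participants will receive the intervention 12 months later". The Aims confirm the crossover of controls: "HAs fitting for controls at 12 months with follow up of 12 months". Both groups are assessed at baseline and at 6, 12, 18 and 24 months, and the text accompanying Fig. 1 separates two analyses: "Primary endpoint analysis at 12 months and follow-up analysis at 24 months are shown in Fig. 1".

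The second-year question is worded at two different strengths:

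- Aims: "We will explore whether the expected clinical gains achieved through the correction of hearing loss by 12 months can be sustained", followed by "if losses experienced through the non-correction of hearing loss can be reversed with the fitting of HAs after 12 months".
- Abstract, Methods: "we will also determine if the expected clinical gains achieved after 12 months can be sustained over an additional 12 months", with the reversal question governed by the same verb.

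The Statistical analysis section says only "We will use multilevel mixed models to investigate changes in cognitive and other scale scores over time" and mentions group-by-time interactions. Nothing in the article calls the month-24 comparison one of early against delayed fitting, or says that the unaided comparator ends at month 12.

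**The concern.** Whether a gain is sustained, or a loss reversed, is a statement about what would have happened without the aids over the same months. For months 12 to 24 no participant is assigned to go without, so that reference is missing by design.

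At stake is what may be concluded. If Group B's scores rise after month 12, the abstract's wording invites a report that late fitting reversed cognitive loss. If Group A's scores stay level, it invites a report that the benefit was maintained. Either would be an uncontrolled before-and-after observation inside a randomised trial, and could be read as having the trial's randomised standing. The Discussion expects the results to move directly into audiology practice, so the distinction matters to readers.

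**Working it through.** The plan gives no figure on this point, so there is none to reproduce. The check asks what the second-year data can identify.

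**Quantities, all for months 12 to 24**

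- s: mean change had participants remained unaided. It includes repeat testing and natural course.
- a: change in A's benefit relative to never being aided.
- b: effect in B of being fitted at month 12.
- E: difference A minus B at month 12.

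**What is observed**, with complete follow-up assumed:

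- Change in A = s + a
- Change in B = s + b
- Difference of the changes = a − b
- A minus B at month 24 = E + a − b

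There are two equations and three unknowns. Randomisation makes s common to both arms, so it cancels in the difference, and a − b is identified: early against delayed fitting. Neither a (sustained?) nor b (reversed?) is identified separately without an assumption about s.

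**Illustration.** Take E = 0.27 SD, borrowing the effect size in the sample-size section. Assume that A changes by 0.00 and B by +0.20 SD over months 12 to 24. The month-24 gap is then 0.27 + 0.00 − 0.20 = 0.07 SD. The value of s is unknown, so a range is shown:

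| Assumed s | a = 0.00 − s | A's benefit at month 24 = 0.27 + a | b = 0.20 − s | Observed gap at month 24 |
|---|---|---|---|---|
| −0.20 | +0.20 | 0.47 | 0.40 | 0.07 |
| 0.00 | 0.00 | 0.27 | 0.20 | 0.07 |
| +0.20 | −0.20 | 0.07 | 0.00 | 0.07 |

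The observed means are the same in every row. In the last row A looks stable although most of its benefit has gone, and B looks recovered although fitting did nothing. In the first row A's benefit has grown.

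**Could s plausibly differ from zero?** The 18- and 24-month visits are at least the fourth and fifth HI-MoCA administrations. The sample-size section allows for 25% attrition. Under the blinding section participants know their allocation, and Group B know that they have just been fitted. Selective dropout and expectation add to the observed changes on top of s.

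**How precise is the identified contrast?** For a plain two-sample comparison without covariates, power = Φ(d√(n/2) − 1.96).

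- With 70 per arm and the full d = 0.27 persisting: 0.27 × √35 = 1.597, so power is Φ(−0.363) = 0.36. If half persists (d = 0.135), power is 0.12.
- With 67 per arm (180 × 0.75 = 135, about 67 each), the values are 0.35 and 0.12.
- The 95% confidence interval with 70 per arm is about ±1.96 × √(2/70) = ±0.33 SD.

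Adjustment for baseline would improve on these figures. They show why a non-significant gap at month 24 should not by itself be read as catch-up.

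**The case against.** The strongest reply is that the Aims already use the modest verb. They reserve *determine* for the 12-month question and use *explore* for the second year, which is defensible for a descriptive aim. This stands, and it places the overstatement in the abstract. It does not make *sustained* and *reversed* identifiable, and the two sections still disagree.

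A second reply is that five visits per arm show more than the month-24 gap: A level with B rising looks different from A falling with B level. The pictures do differ, but the last row of the table shows that A level with B rising also fits waning in A and no effect in B, once unaided scores would have risen. Group B's own unaided first year is a further reference, but using it assumes that practice and decline run at the same rate in both years.

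A third reply is that assessors are blinded and that expectation also affects the first year. Both are true. However, blinding to arm does not hide treated status in a before-and-after comparison within Group B, since by schedule everyone is aided after month 12.

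A reader might go further and infer that the primary result is diluted because a single slope is fitted across all five visits. The article does not support this. It states no linear slope over 24 months, and it places the primary analysis at month 12. How time is coded and which contrasts are reported are commonly left to the analysis plan, which is not shown. Nor does it follow that the second year is uninformative. The arms as randomised can still be compared at month 24, and a persisting gap argues against full catch-up.

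**Conclusion.** The point holds as one about the second-year claim. The abstract promises a conclusion that the two-arm delayed-fitting design cannot give, and it does not match the Aims. No model in an analysis plan can supply the missing comparator; it can only add an assumption about unaided change in year 2. With that change assumed to lie between −0.20 and +0.20 SD, the same illustrative data fit a late-fitting effect anywhere from 0.40 SD to nil, and a month-24 benefit in Group A anywhere from 0.47 to 0.07 SD. That range is an illustration and not an estimate of bias, since the article gives no figure for unaided change.

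The conclusion rests on both arms being assigned aids from month 12 and on there being no third arm; both are stated. The 12-month comparison is untouched. The point should be corrected, but it does not threaten the main result.

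**What to change.** 1. In the abstract, replace *determine* with *explore* for the second-year questions, so that it agrees with the Aims.
2. Define the second-year estimand as early versus delayed fitting. Report A minus B at 24 months, and the change in A minus B from 12 to 24 months, each with a confidence interval. Do not infer catch-up from a non-significant gap.
3. Label within-arm change from 12 to 24 months as descriptive.
4. Do not conclude that gains were sustained or losses reversed without stating the assumption made about unaided change in year 2. Showing the result over a range of that assumption, as in the table, would be enough.

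This needs no new visits, data or participants: a change of wording and contrasts that a group-by-time mixed model can supply. The cost is a more modest claim for the second year, namely whether a 12-month delay in fitting leaves a difference at month 24.

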### Study design

Two-arm parallel randomised controlled trial.

### Participants and setting

We will recruit 180 older adults with mild cognitive impairment and hearing loss. The trial will be conducted at the Ear Science Institute Australia (ESIA) based in the Perth and Bunbury metropolitan regions, Western Australia as well as the Western Australian Centre for Health & Ageing, Perth, Australia. Participants will be recruited from the ESIA hearing clinics, aged-care homes, and hospital memory clinics. In addition, we will place advertisements in the local media and primary care networks, inviting interested participants for screening. If the recruitment of participants is lower than predicted, we will use the electoral roll list to select a random list of people aged ≥70 years living the study areas: they will receive information about the study and an invitation to contact the research office for screening if they believe they may be potentially eligible (the mail out will be de-identified – i.e., investigators will not have access to the list). This approach has been used successfully in other studies.

### Eligibility criteria

Participants will:
Be older adults aged 70 years or older (cognitive decline is more pronounced later in life).Have a Montreal Cognitive Assessment for the Hearing Impaired (HI-MOCA [11] greater than 18 and less than 26 (mild impairment).Have better ear average hearing loss at 0.5, 1 & 2 kHz (3FAHL) > 23 dB or high-frequency average hearing loss (2, 3 & 4 kHz) (HFAHL) ≥ 40 dB as measured using air conduction pure-tone audiometry (HA fitting criteria recommended by Hearing Services Program in Australia for older adults with ARHL [12].Be fluent English speakers.

### Exclusion criteria

We will exclude participants who:
Have impaired instrumental activities of daily living (IADL) [13] due to cognitive deficits (requires assistance or is dependent in the use of telephone, shopping, housekeeping, laundry, transport, management of medications and finances) – i.e. have dementia [14] or major neurocognitive disorder.Meet clinical criteria for cochlear implantation (unaided bilateral sensorineural hearing loss > 70 dBHL, and open-set sentence scores in quiet in the worse ear < 65% and in the better ear < 85% or open set phoneme scores in quiet in the worse ear < 45% and in the better ear < 65% with optimised HA fitting [15].Have visual impairment that limits participant’s ability to read Times New Roman font size 16 (a requirement for two sentences of HI-MOCA).Have a severe medical illness that limits the ability of the participant to attend appointments or sustain participation in the study for 24 months.Plan to move away from the study area during the subsequent 24 months.Are unable or unwilling to provide written, informed consent to participate.Are unable to complete the motor screening task (MOT) module of the Cambridge Neuropsychological Test Battery (CANTAB) due to visual impairment, inability to comprehend test instructions or inability to attend to the task due to dexterity problems [16].

### Intervention

The intervention consists of three parts: (i) hearing assessment and HA discussion, (ii) HA fitting, verification and validation and (iii) HA review following daily use of HAs.

The intervention will be carried out by a qualified audiologist according to the Australian Audiological Society Standards in a standardised soundproof booth. All participants will be given a pair of Oticon OPN 1S hearing aids.

### Outcomes

We will use several well-validated scales to assess our primary and secondary outcomes.

#### Primary outcome measures

*Global cognitive abilities:* Due to hearing impairment, older people may experience difficulty in following verbal instructions or completing tasks that heavily rely on hearing during cognitive assessments. This may result in overestimation of cognitive impairment in such individuals [5]. Hence, we have used a non-verbal global cognitive measure that has been validated to use with the hearing impaired older adults. The global cognitive abilities will be measured using the Montreal Cognitive Assessment for the Hearing Impaired (HI- MoCA [11]. No significant difference was observed for MOCA and HI-MOCA scores in cognitively intact normal hearing participants, and the test-retest reliability coefficient was 0.66 [11].

#### Secondary outcome measures

*Nonverbal cognition assessment using Cambridge Neuropsychological Test Battery (CANTAB)* [16]*- This assessment does NOT rely on verbal communication:*
Attention Switching task (AST): is a test of executive functioning and provides a measure of cued attentional set-shifting [16]. AST is based on the Stroop test and relies heavily on the functions of the anterior right hemisphere and medial frontal structures.Delayed Matching Sample (DMS): assesses participants’ ability to recognise complex visual patterns at different time intervals [16]. It is primarily sensitive to medial temporal lobe dysfunction.Paired Associates Learning (PAL): PAL is a recall test of memory which assesses episodic visuospatial memory, learning and association ability [16]. PAL is primarily sensitive to the changes in medial temporal lobe functioning.Spatial Working Memory (SWM): measures the retention and manipulation of visuospatial information in areas such as non-verbal working memory, working visuospatial memory and strategy use [16].

### Other measures including safety measures

#### General physical & mental health

Participants will be asked to complete the following widely used and validated assessments:
Cognitive reserve questionnaire to obtain information on participant age, gender, education, work history and leisure activities [17].Health status and Quality of life: Short Form survey (SF-12) [18].Physical function: Functional Comorbidity Index (FCI) [19].Depressive symptoms: Patient Health Questionnaire (PHQ-9) [20].Anxiety symptoms: Geriatric Anxiety Inventory (GAI) [21].Function: Lawton & Brody Instrumental Activities of Daily Living (IADL) [22].Social Support and interaction: de Jong Gierveld social support questionnaire [23]^.^Frailty: handgrip strength will be measured using a Jamar Analogue Hand Dynamometer [24].Psychological and social adjustment problems resulting from hearing loss: Hearing Handicap Inventory of the Elderly (HHIE) [25].Effectiveness of the HAs application: International Outcome Inventory for HAs (IOI-HA) [26].Demographic questionnaireHealth-care utilisation cost questionnaire.

#### Hearing Assessment

The assessment of hearing will consist of two parts:
Peripheral hearing assessment will be based on tympanometry, which provides information about middle ear pathologies; pure-tone audiometry, which generates information on hearing thresholds across .25–.8 kHz frequency range; and speech perception in a quiet environment: Consonant-Nucleus-Consonant (CNC) word [27] and City University of New York (CUNY) sentence test [28].Central hearing assessment will comprise of the following tests: Dichotic Digits Test (DDT) [29], Synthetic Sentence Identification with Ipsilateral Competing Message (SSI-ICM) [30] and Quick Speech in Noise (Quick-SIN) [31].

### Procedures for the collection of study measures

The procedure for the data collection will follow the Consolidated Standards of Reporting Trials (CONSORT) guidelines. During the screening process, participants who meet the criteria for inclusion in the study will be randomly assigned to either the experimental (A) or control (B) group. Group A participants will receive the intervention immediately after the baseline assessment, whereas group B participants will receive the intervention 12 months later (Fig. 1). All participants will be informed that if they get randomly allocated to group B, they will have to wait 12 months to receive the treatment. Those who prefer to receive HAs immediately without having to wait 12 months will be given the option to opt-out from the study. Cognition, mental health and QoL assessments will be carried out separately to the hearing assessments and HA fitting.

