### Randomisation, concealment and blinding

The computer-generated randomisation sequence will be stratified by the severity of the hearing loss (mild to moderate vs severe) based on the results of the hearing assessment. Each stratification block will be associated with a random sequence of numbers assigned to the intervention and control group in random permuted blocks of 6, 8 or 10. This sequence will be stored in a password-protected server housed at the University of Western Australia and will be managed by a biostatistician not involved in this project. Once a participant consents and is enrolled, s/he will be automatically ascribed a number and group membership (intervention or control).

Due to the nature of the intervention, participants will know their group assignment, but research staff involved in the assessment of cognitive function, quality of life, mood and physical function will remain blind to treatment allocation. This will be achieved by directing participants to **NOT**: (i) discuss any aspects of the intervention during the assessments, (ii) wear their HAs during the assessment. Binaural hearing amplifiers will be used to facilitate the communication between participants and research staff during all assessment visits (including the 12 and 24-month visits).

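### Allocation is tied to screening and enrolment, with no requirement that the baseline battery be finished first, so participants who know their group can supply baseline data after learning it

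*Protocol article*

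**What the plan says.** All references are to the protocol article.

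- **Time of assignment.** Procedures for the collection of study measures: "During the screening process, participants who meet the criteria for inclusion in the study will be randomly assigned". Randomisation, concealment and blinding: "Once a participant consents and is enrolled, s/he will be automatically ascribed a number and group membership (intervention or control".
- **Place of baseline.** The Procedures section next says: "Group A participants will receive the intervention immediately after the baseline assessment". Group B is treated 12 months later. Both groups have hearing, cognitive, mental health and quality-of-life assessments at baseline and at 6, 12, 18 and 24 months.
- **What must precede assignment.** The sequence is "stratified by the severity of the hearing loss (mild to moderate vs severe) based on the results of the hearing assessment", so hearing is measured first. Eligibility requires an HI-MoCA "greater than 18 and less than 26 (mild impairment", so one value of the primary outcome scale also exists beforehand.
- **Blinding.** The randomisation section accepts that participants know their group. Staff who assess cognition, quality of life, mood and physical function are to stay blind. Participants are told not to talk about the intervention or wear their aids at assessments, and amplifiers are used instead. The Procedures section keeps these assessments apart from hearing assessment and fitting.
- **Hearing-aid measures.** General physical & mental health lists the "International Outcome Inventory for HAs (IOI-HA") together with the SF-12, PHQ-9, GAI, IADL and handgrip. Measuring adherence with treatment has the aid's usage log read at every assessment and a daily diary kept by the participant.

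**The concern.** A baseline is safe to adjust for, or to subtract, because allocation cannot have affected it. That holds if it is measured before allocation, or at least before anyone who could influence it learns the allocation. Here the participant learns it, and many of the baseline measures are self-reports (mood, anxiety, quality of life) or effort-dependent tests (CANTAB). A person who has just learned of a 12-month wait may answer or perform differently from one about to be fitted. The randomised comparison at 12 months would be intact, but subtracting or conditioning on a shifted baseline would carry the shift into the estimate.

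A second, smaller matter concerns assessor blinding. Before month 12 only Group A has trial hearing aids. A completed hearing-aid questionnaire, a listening diary or a connected device, seen by a blinded assessor, would reveal the group.

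**Working it through.** The article states no figure on this point, so the check is one of sequence, followed by an illustration of scale.

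**Step 1: order of events.**

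| Event | Must it precede assignment? | Source |
|---|---|---|
| Consent | Yes | Randomisation, concealment and blinding |
| Hearing assessment | Yes, it defines the stratum | Randomisation, concealment and blinding |
| HI-MoCA for eligibility | Yes | Eligibility criteria |
| IADL and CANTAB motor screening task | Yes, both are exclusion checks | Exclusion criteria |
| AST, DMS, PAL, SWM (CANTAB outcomes) | Not stated | Secondary outcome measures |
| SF-12, PHQ-9, GAI and the other questionnaires | Not stated | General physical & mental health |
| HI-MoCA repeated at the baseline visit, if it is | Not stated | Procedures for the collection of study measures |

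Two sections fix assignment at screening or enrolment. The only sentence that locates the baseline assessment puts it just before Group A's intervention. A site could follow this text exactly and still collect everything in the last three rows after the participant knows the group.

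**Step 2: how a shift reaches the estimate.** Let b be the between-group difference in baseline mean, in SD units, caused by knowing the allocation. Assume that it does not persist to 12 months and that the SD is the same at both times.

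- Change from baseline: absolute bias = b.
- Baseline-adjusted estimate with slope β: absolute bias = β × b.

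The sign depends on which group's baseline moves and in which direction. The article does not say.

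**Step 3: illustration.** b is assumed, since the documents give no value. β = 0.66 is borrowed from the HI-MoCA test-retest coefficient (Primary outcome measures). It is not a baseline-to-12-month slope and need not apply to CANTAB or the questionnaires. The design effect d = 0.27 (Pilot test and sample size) serves only as a yardstick.

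| b (assumed) | Change score | As share of 0.27 | Adjusted, 0.66 × b | As share of 0.27 |
|---|---|---|---|---|
| 0.05 | 0.05 | 0.05/0.27 = 19% | 0.033 | 12% |
| 0.10 | 0.10 | 0.10/0.27 = 37% | 0.066 | 24% |
| 0.20 | 0.20 | 0.20/0.27 = 74% | 0.132 | 49% |

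**Step 4: hearing-aid measures against the blinding text.** The IOI-HA sits in a list that also holds the measures taken by blinded staff, and it is absent from the separate Hearing Assessment list. No visit, group or administrator is given for it. Reading the device log at every assessment fits the blinding safeguards only if the hearing sessions are meant. The article does not say so.

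**The case against.** **The order is partly inferred.** No sentence says that baseline follows disclosure of the group, and the flowchart (Fig. 1) and timeline (Table 1), which may settle it, are not shown. This stands as a limit on certainty. It does not remove the need for the text to state the order, since two sections place assignment early and neither makes it conditional on baseline.

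**The primary outcome has a value from before allocation.** This stands. Every randomised participant has an eligibility HI-MoCA. If that score is the baseline, the primary contrast is protected. The article does not say that it is, and it lists a cognitive assessment at baseline.

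**The IOI-HA list is an inventory, not a schedule.** This also stands. A reader might infer that assessor blinding is broken at 6 and 12 months because only Group A can complete the form. The documents do not support that. Hearing-aid effectiveness is not among the domains assigned to blinded staff, the form may already belong to the separate hearing session, and the stated safeguards are real. What remains is a possible route to unblinding that the text leaves open.

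**The opt-out.** People who do not want to wait "will be given the option to opt-out from the study". A reader might infer that participants already assigned to Group B can leave before baseline, with losses in one arm only. The wording is conditional and addressed to all participants, and reads naturally as information given before allocation. It does not support a claim of one-sided loss.

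**Conclusion.** The point holds in limited form. As written, the article allows baseline CANTAB, mood, quality-of-life and other self-reported measures, and any repeated HI-MoCA, to be collected from participants who know their group. This threatens change-from-baseline and baseline-adjusted contrasts, mainly for secondary outcomes. The primary outcome is exposed only if a HI-MoCA taken after allocation is used as its baseline.

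The magnitude is unknown. The range of 0.05 to 0.20 SD for change scores, or about 0.03 to 0.13 SD after adjustment, rests on an assumed shift, an assumed slope of 0.66 and the assumption that the shift does not persist. It shows that a modest shift would not be negligible beside 0.27, and it is not an estimate of what will happen. That participants know their group at 12 months is unavoidable and openly acknowledged, and is not part of this point. The hearing-aid measures are an inconsistency to tidy, not a demonstrated breach of blinding.

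**What to change.** 1. State that the server releases group membership only after consent, the hearing assessment and the complete baseline battery are recorded. Bring the Procedures and Randomisation sections into line with this.
2. If that order cannot be kept, name the pre-allocation screening HI-MoCA as the baseline for the primary outcome. This protects the primary contrast only. The secondary measures would still be exposed.
3. State that the IOI-HA, the listening diary and the hearing-aid data log are collected at the separate audiology session, away from the blinded assessors. The outcome list and the adherence section would then agree with the blinding section.

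The cost is a reordering of existing steps and a few sentences of text. Hearing sessions are already separate from the cognitive, mental health and quality-of-life assessments, so no new visit or measure is needed.
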